### 10.3.1 Foreseeable adverse events/anticipated adverse device effects

As this is the first study to evaluate the safety and performance of the GS2 device in humans, we do not yet know the likely incidence of the anticipated adverse device effects. Therefore, we have listed the anticipated ADEs below, based on the risk management report performed in accordance with ISO 14971:2019. The probability of occurrence of the hazardous situation and the probability of severity level have been estimated in accordance with the residual risk assessment of the risk management report.

| Anticipated ADEs                                | Probability of Severity Level (S) | Probability of Occurrence of a Hazardous situation (O) |
|-------------------------------------------------|-----------------------------------|--------------------------------------------------------|
| Metabolic and nutritional disorders      |                                   |                                                        |
| Hypoglycemia event ( $\leq 3.2$ mmol/l)         | Negligable to critical (S1-4)     | Remote to Frequent (O2-5)                              |
| Hyperglycemia event ( $\geq 8.5$ mmol/l)        | Negligable (S1)                   | Remote to Occasional (O2-3)                            |
| Malnutrition: Short-term over-nutrition         | Minor to Serious (S2-3)           | Occasional (O3)                                        |
| Malnutrition: Short-term under-nutrition        | Minor to Serious (S2-3)           | Probable (O4)                                          |
| Malnutrition: Over-nutrition                    | Minor (S2)                        | Occasional (O3)                                        |
| Malnutrition: Under-nutrition                   | Minor (S2)                        | Occasional (O3)                                        |
| Gastrointestinal disorders               |                                   |                                                        |
| - Digestive disorder such as vomiting, diarrhea | Minor to serious (S2-3)           | Occasional (O3)                                        |

For all ADEs listed above, risk mitigation was performed as described in the risk management report. For example, for hypoglycemia, the interval until the next BG measurement was shortened in certain situations. In addition, the maximum increase in insulin dose was limited, and some written comments were made to raise user awareness.

### 10.3.2 Reporting of (Serious) Adverse Events, device deficiencies, and other safety related events

#### Procedure for the user to report unexpected/alarming results or problems:

This procedure has been described in the "Instruction for use" (GS2-IFU\_V1.1). In case of unexpected/alarming results or problems, one of the study investigators will analyze the situation and fill out the device deficiency form if needed and inform the principal investigator (PI) of the study. The PI will decide whether the device deficiency requires a suspension of the study until the manufacturer has taken preventive or corrective actions. All information about the device deficiency will be collected and the manufacturer will be notified within 24 hours of working days. The manufacturer assumes the responsibility to carry out necessary steps and corrective measures.

Suspected device deficiencies fall into one of the following 4 categories:

- 1) Unexpected behavior/suspected errors
- 2) Advice that is not compatible with departmental guidelines
- 3) Slow performance
- 4) Malfunction/ reliability issues

In general, if a device deficiency is observed or suspected, one of the investigators should be contacted not later than 12 hours after the observance.

It is recommended, that the user acts according to the following schema:

| Suspected device deficiency                                                                                                                                                                                                                                                                                                                                                                                                                                                                                                                   | Procedure                                                                                                                                                                                                                                                                                                                                                                                                                                                                  |
|-----------------------------------------------------------------------------------------------------------------------------------------------------------------------------------------------------------------------------------------------------------------------------------------------------------------------------------------------------------------------------------------------------------------------------------------------------------------------------------------------------------------------------------------------|----------------------------------------------------------------------------------------------------------------------------------------------------------------------------------------------------------------------------------------------------------------------------------------------------------------------------------------------------------------------------------------------------------------------------------------------------------------------------|
| 
1) Unexpected behavior/suspected errors:
 
Examples:
 

- No new nutritional target is calculated by GS2, even though the Nutritional Targets page was just visited by the user

- Entering the ID of a patient into GS2 prompts GS2 message that "The ID cannot be found" even though the ID is known to be correct

- GS2 notifies the user that there is a new Indirect Calorimetry measurement available when no indirect calorimetry was done recently

            | 
Take a note of the situation (which patient, date & time of the observed behavior, description of the behavior, screenshot of GS2 if possible).
 
The user should discuss the note with one of the investigators during the daily visit.
 
The PI will decide if it is a device deficiency.
                                                                                                                                                           |
| 
2) Advice that gives rise to concern:
 
Examples:
 

- Insulin dose (<math>> 0</math> U/h) is advised when blood glucose is below target (5 - 8.5 mmol/l) and the patient is not insulin-dependent chronically diabetic.

- Glucose bolus injection is advised when patient's blood glucose is not hypoglycaemic.

- No nutrition advised for a patient on the fourth day in the ICU.

- GS2 advises to increase insulin in a single step larger than 2 U/h.

 | 
Refuse the advice given by GS2 until the PI or co-investigators have been consulted.
 
Take a note of the situation (which patient, date & time of the observed behavior, description of the behavior, screenshot of GS2 and of the advice window).
 
Contact the investigator immediately, not later than 12 hours after the observance.
 
The PI will decide if it is a device deficiency and if a suspension of the study is required.
 |
| 
3) Slow performance
 
Examples:
 

- Waiting time after a requested advice exceeds 20s until advice window opens.

                                                                                                                                                                                                                                                                                                                                                                    | 
Slow performance can be expected if a large amount of data of the patient has to be loaded, but it could also be either a device deficiency, or a failure of the external patient data management system Clinisoft.
                                                                                                                                                                                                                                                 |

|                                                                                                                                                                                                                                                                                                                                                                                                                                                                        |                                                                                                                                                                                                                                                                                                                                                                                                                        |
|------------------------------------------------------------------------------------------------------------------------------------------------------------------------------------------------------------------------------------------------------------------------------------------------------------------------------------------------------------------------------------------------------------------------------------------------------------------------|------------------------------------------------------------------------------------------------------------------------------------------------------------------------------------------------------------------------------------------------------------------------------------------------------------------------------------------------------------------------------------------------------------------------|
| 
 
- Waiting time to load a new patient from Clinisoft exceeds 2 minutes.
 
 
Waiting time for "Nutritional Targets" page, "Advice" Page, and "Patients" page exceeds 30s
                                                                                                                                                                                                                                            | 
Take a note of the situation (which patient, date & time of the observed behavior, description of the behavior, screenshot of GS2 if possible). Please add a description of how you interacted with GS2 and what the approximate time of waiting was.
 
The user should discuss the note with one of the investigators during the daily visit.
 
The PI will decide if it is a device deficiency.
 |
| 
4) Malfunction/technical issues:
Examples:
 
 
- Import of the patient's data from Clinisoft is incomplete (data shown in Clinisoft are not visible in GS2)
 
- Data "out-of-range" messages appear when entered data are correct, for example "75 kg is not a correct body mass"; "2345 kcal is not a correct energy expenditure"
 
- Graphical user interface freezes and inhibits use of GS2
 
 | 
The user should stop using GS2 until the investigator has been informed.
 
Meanwhile, take a note of the situation (which patient, date & time of the observed behavior, description of the behavior, screenshot of GS2 if possible).
 
Contact an investigator immediately.
                                                                                                                      |

### **Reporting to the Sponsor:**

Reporting to Sponsor-Investigator:

The following events are to be reported to the Sponsor-Investigator within 24 hours upon becoming aware of the event:

- All reported SAEs
- Health hazards that require measures
- Device deficiencies

The Sponsor-Investigator will evaluate SAEs regarding causality and seriousness. Device deficiencies are assessed regarding their potential to lead to an SAE. The Sponsor will decide if the device deficiency needs a suspension of the study until a preventive or corrective action has been taken by the manufacturer (refer to GS2-IB, point 5.1).

### **Reporting to the manufacturer:**

According to the contract regarding risk management, any device deficiency will be reported by the PI to the manufacturer. An electronic notification will be sent directly to the manufacturer when a device deficiency form is entered in the eCRF in secuTrial®. The PI will then confirm the good reception of the notification with the manufacturer within 24 hours. The manufacturer undertakes the responsibility to perform necessary updates to risk analysis, to the device itself, to the GS2-IB and to inform the Sponsor-Investigator of any corrective action taken.

### **Reporting to the Competent Ethics Committee and to Swissmedic:**

Reporting of events to the Competent Ethics Committee and to Swissmedic will be subcontracted to the pharmacovigilance team of the UIC (Unité d'Investigation Clinique), a unit of the CRC (Centre de Recherche Clinique/CTU) at HUG.

The following events are to be reported to the CEC and to the CA promptly (Art. 33 ClinO-MD) [4]:

- a. any serious adverse event which has a causal relation with the MD, comparator or procedure/test method or where a causal relation is probable or possible (SADE);
- b. any device deficiency which, in the absence of appropriate measures or intervention or in less favourable circumstances, could have led to serious adverse events (DD with SADE potential);
- c. any new information relating to an event already notified under points (a) and (b).

To ensure prompt notification, the Sponsor may initially submit an incomplete notification.

If safety and health hazards that require measures must be taken immediately during the conduct of the investigation, the Sponsor notifies the CEC within 2 days of these measures and the circumstances which made them necessary (Art. 34 ClinO-MD) [4].

Periodic safety reporting (Art. 35 ClinO-MD) [4]:

An Annual Safety Report (ASR) is submitted by the Sponsor to the CEC and to the CA, yearly (Art. 35, 38 ClinO-MD) [4]. The ASR contains a list of all SADEs and DDs and a report on their degree of seriousness, causal relationship with the MD and procedure and on subjects' safety.

### **10.3.3 Follow-up of (Serious) Adverse Events**

All patients with reported AE or SAE will be followed during the entire study period (from patient's informed consent until the end of the ICU stay or the end of the 15 days of follow up) [ISO 14155]. SAEs will be followed until resolution or stabilization. Participants with ongoing SAEs at study termination (including the closing visit) will be further followed up until they recover or until stabilization of the disease.

## 11. STATISTICAL METHODS

### 11.1 Hypothesis

The null hypothesis is that the mean time in target glycaemia (defined as BG between 5 and 8.5 mm/L) will be equal between patients randomized in the intervention arm and in the standard of care arm (control group).

Alternative hypothesis is that the mean time in target glycaemia will be different between patients randomized into the intervention group and into the standard of care group (control group).

### 11.2 Determination of Sample Size

Based on data collected routinely at the ICU between January and March 2017, the time in target was 68% (SD 21%) for patients under the standard of care. Expecting the intervention to give an improvement of 10% of time in target, we would need 71 patients in each patient group to detect give the trial a power of 80% and an alpha error of 5% (two-sided). If the patient refuses to participate afterwards or withdraws from the study for whatever reason, they will be replaced in order to have 71 per group at the end of the study.

### 11.3 Statistical criteria of termination of the investigation

Patients will be followed until the end of ICU stay or before, if the standard of care naturally ends.

### 11.4 Planned Analyses

Continuous variables will be presented according to the study group by their mean ( $\pm$ standard deviation SD), median, interquartile range and range. Categorical variables will be presented according to the study group by their frequencies and relative proportions.

#### 11.4.1 Datasets to be analysed, analysis populations

The dataset from intervention group will be analysed against both the control group and the historical control group. To assess a possible “cross-over” effect, the control group will be analysed against the historical control group. All analyses will be performed in an intention-to-treat basis: all patients will be analysed as randomized.

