### **2.7.1 Request for authorization under Article 34 of the HRA**

For the participants in the retrospective control group, we ask for permission to use the data without the patient's consent in accordance with Article 34 of the HRA [7]. In fact, we want to analyse 71 data files from patients who were admitted to the ICU within 2 years before the start of the study. The process of obtaining post-hoc consent would be extremely complex as ICU mortality can be as high as 20%. The exclusion of patients for whom we cannot obtain consent would lead to a selection bias.

The project sponsor/investigator confirms that no patient health-related data will be utilized in this study from patients that refused participation (in written or documented oral refusal) in research studies.

Important information regarding informed consent and the use of collected data:

- If the participant or representative refuses post-hoc or proxy consent, the participant will be withdrawn from the study. The data collected so far will be destroyed and will not be analysed (ClinO Art. 17, alinea 3) [8]. If a participant or representative withdraws his/her consent, the same process will apply.
- If no representative is identified and no proxy consent could be obtained, the patient will be withdrawn from the study and his/her data will be destroyed and will not be analysed. If the patient recovers his/her capacity to consent and declines to give consent, he or she will be withdrawn from the study and the procedure outlined above will apply.
- If a participant already enrolled in the study dies before consent or refusal could be obtained from him/ her or a representative, the personal health information collected may be used only if the participant has consented to the use of his/her personal health data for research purposes in an advance directive or other form.

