### 7.4 Criteria for withdrawal / discontinuation of subjects

Once started in either intervention or control arm, the study protocol will continue until one of the following circumstances is encountered:

- 1- Death; or
- 2- Withdrawal of life support; or
- 3- Consent withdrawal

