### **9.2.5 Assessments in subjects who prematurely stop the clinical investigation**

For the patients prematurely withdrawn of the study, no follow up is planned. The data collected so far will be destroyed and will not be analysed (OClin Art. 17, alinea 3) [8] (see point 2.7 for more details).

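### The protocol promises intention-to-treat, but its consent and replacement rules leave only randomised patients with usable consent in the analysis

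*Protocol*

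**What the plan says.** - **Analysis population (Protocol 11.4.1):** "All analyses will be performed in an intention-to-treat basis: all patients will be analysed as randomized".
- **Replacement (11.2):** "If the patient refuses to participate afterwards or withdraws from the study for whatever reason, they will be replaced", so that each group ends with 71.
- **Data of patients who leave early (9.2.5):** no follow-up is planned and "The data collected so far will be destroyed and will not be analysed". The sentence cites Article 17 of the clinical trials ordinance and sends the reader to section 2.7.
- **Consent (2.7.1):** citing the same article, it applies the same destruction rule when post-hoc or proxy consent is refused and when consent is withdrawn. It adds: "If no representative is identified and no proxy consent could be obtained, the patient will be withdrawn from the study", again with destruction of the data. If an enrolled patient dies before consent or refusal is obtained, the data may be used only if the patient had earlier agreed to research use.
- **Withdrawal criteria (7.4):** "Once started in either intervention or control arm, the study protocol will continue until one of the following circumstances is encountered". The list that follows is death, withdrawal of life support and consent withdrawal.
- **Discontinuation (8.2):** the same three events are described as ending the intervention.
- **Context:** the trial is unblinded (6.1), most patients cannot consent at inclusion (2.7), and no specific method for missing data is planned (11.5).

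**The concern.** Patients whose records are destroyed, and whose places are then filled by others, cannot be analysed as randomised. The statement in 11.4.1 is therefore not true of the trial as planned, and a statistical analysis plan could not repair it, because destroyed data cannot be recovered.

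The loss need not be balanced. Most patients enter on a proxy's consent or an independent physician's authorisation, so the consent decision that fixes whether their data survive comes after inclusion. By then the arm is known and part of the clinical course has been seen. If refusal, or failure to obtain consent, is linked to both, the comparison of time in target no longer has the protection of randomisation.

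The protocol recognises the mechanism. In 2.7.1 it argues, for the historical controls, that leaving out patients whose consent cannot be obtained would cause selection bias, and it asks for a waiver on that ground. The randomised arms lose such patients and the historical group, documented refusals apart, does not. Yet 11.4.2 allows a superiority conclusion against either comparator.

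**Working it through.** **1. The passages side by side.**

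| Event after randomisation | Data | Replaced under 11.2? | Analysed as randomised? |
|---|---|---|---|
| Consent refused or withdrawn | Destroyed (2.7.1, 9.2.5) | Yes | No |
| No proxy consent obtained | Destroyed (2.7.1) | Yes, if being withdrawn counts as withdrawing | No |
| Death before consent or refusal | Usable only with earlier agreement to research use (2.7.1) | Not stated | Only in part |
| Death or withdrawal of life support, consent valid | 8.2 and 2.7.1 suggest kept; 7.4 read with 9.2.5 is unclear | Unclear | Unclear |

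The first two rows contradict 11.4.1 outright, the third does so in part, and the fourth is an ambiguity.

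**2. The sample size, reproduced.** Inputs from 11.2: "the time in target was 68% (SD 21%) for patients under the standard of care"; a hoped-for gain of 10%; power 80%; two-sided alpha 5%; 71 per group.

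- Normal approximation: n = 2 × (1.960 + 0.842)² × 21² / 10² = 69.2, so 70 per arm.
- Noncentral t: 70.2, so 71 per arm, as stated.
- Power at 71 per arm: 0.810 (normal) or 0.804 (t).
- The 10% must mean 10 absolute points. A relative 10% is 6.8 points and would need 150 per arm.

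The arithmetic is sound. The 71 contains no allowance for losses, because replacement is meant to cover them. Replacement restores the number of patients but not their comparability.

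**3. Illustrative size of the bias.** Suppose removed patients have a mean time in target D points below those kept, with the same D in both arms, and that the proportions removed differ between arms by w. Then

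bias in the mean difference = w × D.

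The protocol gives neither w nor D, so both are assumptions. For the two-sided type I error, take equal true means, SD 21 and 71 per arm. Then SE = 21 × √(2/71) = 3.52, and

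type I error = 1 − Φ(1.96 − bias/SE) + Φ(−1.96 − bias/SE).

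| w (assumed) | D (assumed) | Bias, points | Share of the 10-point effect | Type I error |
|---|---|---|---|---|
| 5% | 10 | 0.5 | 5% | 0.052 |
| 5% | 20 | 1.0 | 10% | 0.059 |
| 10% | 10 | 1.0 | 10% | 0.059 |
| 10% | 20 | 2.0 | 20% | 0.088 |

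The direction depends on which arm loses more patients with poor control. If removal is equal in both arms and D is the same, the bias is zero.

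**The case against.** Destruction after refusal is presented as a legal requirement, so respecting it is not a design fault. That stands: the fault is the unqualified intention-to-treat label together with replacement. It is also fair that reporting of exclusions per arm often belongs in a statistical analysis plan, which is not shown. The population statement and the replacement rule, however, are fixed in the protocol.

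Four stronger readings are tempting, and the documents do not carry them.

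- *That all deaths and withdrawals of life support are erased and replaced.* A reader could infer this from 7.4, 9.2.5 and 11.2 taken together. But 9.2.5 cites the same article as 2.7.1 and refers back to 2.7, where destruction follows only from consent. Section 8.2 treats these events as ending the intervention. The special rule in 2.7.1 for death before consent would be pointless if every death led to destruction, and 9.2.6 and 9.3.4 record alive status. Ambiguity is all that remains.
- *That the 20% ICU mortality in 2.7.1 is a loss rate for this trial.* It is an upper figure, given to justify the waiver for the historical group.
- *That a destroyed record could decide the hypoglycaemia stopping rule.* The criteria in 1.6 and 2.9 operate during the trial, serious adverse events reach the sponsor within 24 hours (10.3.2), and nothing says that a later refusal reverses an event already counted.
- *That refilling to 71 per group forces allocation by arm.* The list can be continued until each arm has at least 71, and nothing in 7.3 permits choosing the arm. The protocol simply does not say how replacement is to be done.

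**Conclusion.** The contradiction holds for consent-based loss and needs no inference: 11.4.1 cannot be true alongside 2.7.1, 9.2.5 and 11.2. The handling of death and withdrawal of life support is ambiguous, and 7.4, 8.2, 9.2.5 and 11.2 must be reconciled. Under the assumed ranges above, the bias is 0.5 to 2 points, or 5% to 20% of the design effect, with type I error of about 0.052 to 0.088. These figures rest on assumed differences between arms and an assumed common gap. They show what is possible, not what is expected. The sample size calculation is not at fault. This should be fixed; it does not by itself invalidate the trial.

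**What to change.** 1. In 11.4.1, define the population as all randomised patients whose data may legally be used, analysed in the arm to which they were randomised. State that removals and their reasons will be reported per arm.
2. In 7.4, 9.2.5 and 11.2, state that death and withdrawal of life support end follow-up, that data up to that point are kept where consent is valid, and that these patients are not replaced. Keep the rule in 2.7.1 for death before consent as a separate case.
3. In 11.2, drop the refilling to 71 per group. Continue the existing stratified randomisation list until 142 patients with usable data are included, and accept slightly unequal arms.

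The cost is amendment wording. Unequal arms cost almost nothing: with 70 and 72 patients, SE = 21 × √(1/70 + 1/72) = 3.52, the same to two decimals as with 71 and 71. The number to randomise is essentially what replacement already implies: for assumed losses of 5% or 10%, 142/0.95 = 150 or 142/0.90 = 158 in total. None of this removes selection from refused consent. It names the population correctly and lets readers see the loss in each arm.
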